## Abstract

**Background:**

The prevalence of childhood obesity increased worldwide in recent decades and is associated with risk factors for the development of chronic diseases in adulthood. Strategies for health promotion directed at an early age, with recommendation for healthy habits, can achieve good results. The objective of this study is to evaluate the effectiveness of an innovative, simple and cost effective educational program to improve eating habits, physical activity and the knowledge about healthy habits in children, as well as in their families, as compared to routine outpatient care.

**Methods/Design:**

The study is designed as a randomized clinical trial. Sample size is estimated to include 37 children, aged between 7 and 11 years, and their guardians, randomized for an intervention or a control group. The intervention will consist of 11-weekly group meetings of nutritional education and distribution of explanatory material, with orientation about healthy food and family habits and physical activity. Recreational, simple and low cost resources, carefully designed for the presentation of contents to the children and parents, will be used in all meetings. The control group will receive standard outpatient care based in individual clinical practice guidelines. The primary outcomes will be changes in dietary habits, knowledge and physical activity of children and adults. The secondary outcomes will be changes of body mass index, waist circumference, systolic and diastolic blood pressure and laboratory tests, in children and adults.

**Discussion:**

The Happy Heart Study offers a playful and low-cost approach for the prevention and control of obesity and cardiovascular disease in children. Although this program is being planned for implementation in Brazil, the method can be adapted to many other countries.

**Registry of protocol:**

Protocol registered on the site ensaiosclinicos.gov.br: RBR-8ttw64.

## Background

The global incidence of childhood obesity in recent decades has been considered as a worldwide epidemic, present in all socioeconomic classes, age and ethnical groups [1]. Although this incidence has plateaued in many developed countries, it is still increasing in many parts of the world [2-4]. Children with excess weight are at a greater risk of obesity in adult life. In a cohort that included 1709 overweight 5–12 year-olds, almost half of the girls and a third of the boys became obese adults before the age of 40. Of those with more than 12 years old, 60% remained obese in adulthood [5]. A systematic review showed that overweight children had twice the risk of becoming overweight adults, compared with healthy weight children [6].

Poor lifestyle habits, such as consuming processed foods, with high sugar, fat and sodium content; reduced consumption of fruits and vegetables; sedentary activities such as long periods spent watching on TV or at the computer; all contribute to the continuing increase in the prevalence of overweight among children [7-10].

Previous studies have shown that the habit of watching more than two hours of TV a day is associated with an unfavorable body composition [10] and may affect physical and psychological health. Decreased levels of physical fitness, low self-esteem, social behavior change and lower levels of academic achievements have been related to screen time [11].

Conversely, changes in lifestyle, including decreasing screen time, reducing consumption of fat-rich foods and reducing physical inactivity may lead to decreased body mass index (BMI) [11,12].

Childhood is considered as a critical period, during which the patterns of dietary habits and lifestyle are learnt and rooted [13,14]. The fact that, in this age group, the control over eating habits is still largely dependent on the parents makes the treatment more complex, since success depends on involving the family in the whole reeducation process [11,15-17]. Results of a meta-analysis revealed that interventions that included family members produced larger effects than interventions focusing only in children [18,19].

Therapeutic groups represents another important option, since they promote and enhance the process of health education. Problems are divided among the group components and solutions are sought collectively, helping to achieve the bigger objective which is the change in behavior, both for the family and the child [17-19].

There is evidence that social support helps to improve lifestyle habits. Many patients find the motivation and energy required to maintain healthy eating plans through the support of their peers. Group support is one of the most valuable ways of support, especially regarding motivation [11].

Preventive interventions, including health education strategies to reduce obesity and other cardiovascular risk factors in children, are important tools for the reduction of the epidemics cardiovascular diseases in the future [20-22]. Educational programs focusing in food habits are being implemented in various countries [23-25], but studies on interventions to reduce cardiovascular risk factors in childhood in the routine pediatric ambulatory are still scarce [26,27].

A systematic review and meta-analysis conducted by our group showed that education and physical activity interventions in children have good results on blood pressure control and biochemical parameters [28], however, there is little effect an antropometric measures [28].

Individuals develop theories to explain experiences and discuss concepts from observations and analyzes, thus systematizing their knowledge. The information in itself is not enough to change habits and attitudes; only when the individual gives sense to the information that it becames knowledge, which can lead to an attitude change. Knowledge is processed and acquired from several ways, depending on the context, the time, the emotional status and motivation of individuals. It is noteworthy that perception is influenced by socio-cultural habits and by the personality of the perceiver, which determine how the individual sees, hears, thinks, acts and feels [21].

Scholars in the field of education explain the construction of knowledge in several ways. In accordance with the Swiss educator Jean Piaget, the development of intelligence in children is based on an approach that considers knowledge a result of subject-object interaction [29]. The subject learns by his actions, as he/she builds his knowledge from interactions with the environment. Development is an ongoing and always expanding process [29]. Russian neuropsychologist Lev Vygotsky believed that education and knowledge building take place within a cultural-historical context. Thus, knowledge building occurs through experiences and habits, attitudes and values of those who interact with the child in his family group and in their living group. Therefore, it is in the intra- and interpersonal relationships that the subject will internalize the knowledge of social roles and functions [30]. For the researchers Maturana [31,32] and Varela [33], life is a continuous process of knowledge. Educating constitutes a process during which the individuals live with one another, constantly adjusting this coexistence in a way in which makes progressively more congruent with each other in the living space. Learning happens, therefore, all the time and in a reciprocal way [31-33]. For Freire, the maturation of new possibilities and new challenges occurs through the exploitation of the environment; the subject builds new answers, and the construction of knowledge occurs through interaction with the world. The knowledge of the child in early childhood is based on the observation of the attitudes of adults. Bridging this concept to health education in childhood, playful activities are very effective in the teaching-learning process, arousing curiosity and facilitate the child’s understanding [34]. The pedagogical workshops can serve as catalysts for construction of collective/individual creative knowledge. Every workshop needs to promote search, action and reflection, combining individual and collective work and ensuring the unity of theory and practice [29,32].

A study developed in Brazil with children 5 – 10 years-old and their teachers showed that, after nutritional interventions, there was an increase in students’ knowledge from 61.1% to 73.6%; teachers also showed a significant increase in their knowledge [21]. The same was found in the 464 children, with the use of a Cognitive Theory based programme [34]. Studies based in interventions designed to increase knowledge of patients with chronic diseases showed increased knowledge and improved self-care of these individuals [35,36]. Thus, increasing knowledge may help to improve self-care related to life habits changes.

In this context, the present study aims to present a differentiated proposal that includes technological resources that are already part of the lives of young people. The target population is formed by schoolchildren, also called “digital natives”. The construction of learning in a healthy education should involve attractive tools, in accordance with the reality of the world in which they live, in order to reach a more effective practical modification of life habits [28,37,38].

This proposal aims to work with a mixture of low cost and innovative materials, associating recreational activities with everyday knowledge of the participants and scientific knowledge of professionals involved, through the formation of a group (children and parents) in which participants can share experiences [11-15]. It is a proposal involving collective construction of healthy habits, with the potential to reach a large number of people, thus reducing expenses with the consequences of future chronic diseases [22,23].

In addition, the use of a multidisciplinary educational intervention protocol for prevention of chronic diseases, guiding the child and family toward the construction of a critical, conscious and healthy thinking, can allow the individual to multiply the knowledge among family, school, work and community as a whole. After validation by the present study, this protocol may be used in different settings (school, family health strategy, community centers), allowing the prevention of chronic diseases through an educational program.

Thus, our hypothesis is that an educational program with playful activities for children and families, including text message reminders and social media composed of recreational activities is effective to increase the knowledge, physical activity and improve cardiovascular risk in children with risk factors, when compared to usual outpatient management. The objectives of the study are evaluate the effectiveness of an innovative, simple and cost-effective educational program in improving eating habits, physical activity and the knowledge of healthy habits in children, as well as their families, compared to routine ambulatory medical care.

## Methods/Design

### Study design

The study is planned as a randomized controlled, outcome evaluator-blinded parallel prospective clinical trial. This protocol is based in the CONSORT and SPIRIT statements for reporting of clinical trials and protocols [39,40]. A total of 74 children will be recruited. After the initial assessment, children will be randomized to either the intervention or the control groups with 1.1 allocation (Figure 1). The study setting is the “Instituto de Cardiologia do Rio Grande do Sul”, a cardiology hospital in south Brazil.

**Figure 1 Fig1:**
[figure not shown]
**Flow chart: study design.**

### Participants and recruitment

Patients will be recruited through public announcements in radio and newspapers of wide circulation in the State of Rio Grande do Sul, and through referrals by health professionals from the public health system. All children and their guardians will be informed about the goals and methods of the study. Parents and children who meet the inclusion criteria and agree to participate in the study will sign an informed consent.

### Inclusion/exclusion criteria

Inclusion criteria are: Children aged 7 11 years presenting at least one of the following risk factors: overweight or obesity, hypertension, dyslipidemias or diabetes.

Exclusion criteria are: contraindications for the practice of physical activity, use of drugs that would interfere with body weight and/or lipid profile and neurological or cognitive deficits that would prevent the completion of questionnaires.

### Interventions

The goal of the intervention is to improve health habits of students and their families. Children and their families will receive intervention for eleven weeks. The materials will be developed around the following key messages:Consequences of inadequate eating habits;Recommendation of adequate intake of nutrients;Health promotion strategies.

The materials will be designed for a fun, entertaining appearance. The meetings will be practical and playful, including culinary workshops, games and homework assignments. All materials were developed targeting this specific cultural environment, based on our 10-year work with children in the Public Health System in Brazil. We have researched materials from other countries, but we felt that developing our own materials would benefit other groups in similar situations. We also plan to involve the children in the creation of materials during the workshops. Materials are fun and playful because they are mostly based in popular games and ludical activities. Workshops will be held in 3 different days of the week, from 6 PM to 7:30 PM. The setting is a health school located in the complex of Instituto de Cardiologia, with an ample room to accommodate children and families. All the members of the family that wish to participate together with their children will be invited. Children and caretakers will attend the workshops together, except in the days when the cooking workshops will take place at the cooking lab (days 3 and 8). During the 9 weeks of workshops, text messages will be sent twice a week, on Mondays and Saturdays (total of 18 messages). Message content will be related to practical tips for a healthy lifestyle. Some examples are presented in Table 1.

**Table 1 Tab1:** **Examples of text messages for families**

**Number**	**Message**
1	Remember to eat vegetables today and everyday!
2	Eat slowly and enjoy your food!
3	Avoid soft drinks; substitute for a nice up of water :-)
4	Water is important for the organism to work well; remember to take a glass now!
5	How about turning off the TV now and go for a family walk?
6	Use different vegetables. An idea: grate a red cabbage and a carrot; add an apple and season with olive oil, balsamic vinegar and black pepper.
7	The way food is introduced to kids is very important, as this may determine if he/she will accept it or not. Even when the child refuses the food, you may try another way to introduce it. Do not give up!
8	To stimulate children to practice sports is a key factor in the fight against childhood obesity and other diseases.
9	The best strategy to make a sandwich tastier, nutritive and less caloric is to increase leafs and vegetables among its ingredients. Green leafs, as lettuce, spinach and vegetables such as tomatoes, carrots, beet, green pepper and hearts of palm fill your sandwich, giving a sturdy appearance to the snack and, at the same time, promoting greater satiety.
10	Try to use less salt in your food and remove the saltshaker of the table. Avoid consuming industrialized food with lots of salt, like hamburgers, sausage, ham, pretzels, canned vegetables, and manufactured soups, sauces and seasonings.

After the end of each workshop, the participants will receive information about the importance of healthy practices for cardiovascular health and homework assignments (painting, collages, games, creating stories and drawings), in order to improve awareness and encourage the correct choice of foods to improve lifestyle. Text messages with motivational phrases will be sent to the parents during the week and, in the days prior to meetings, they will be reminded of the local and time of activities, in order to stimulate attendance. In addition, a closed group will be created on the social network Facebook, for sharing experiences, exchanging recipes, questions, progress and suggestions, thus strengthening the link between patients and professionals.

A total of 11 meetings will be held. The first and the last meetings will be used for nutritional and biochemical assessment and the nutrition education program will be developed during the remaining nine meetings with 90-minute weekly workshops, summing up a total of eleven weeks of participation. The activites will be deleveloped as part of the educational program, as shown in Table 2.

**Table 2 Tab2:** **Activities to develop in the educational program**

**Meeting**	**Description of workshops**
1	Food pyramid class. The food pyramid will be explained with an acrylic pyramid and life-size food replicas. The importance of a healthy and balanced diet will also be emphasized. This concept will be illustrated with replicas of an artery for visualization of the effects of a diet rich in fats, sodium and sugar in the blood vessels. Other subjects discussed in this meeting will include the dimension of portions, plates, glasses, cups and other kitchen utensils, in order to teach about the proper amounts for the age group. Children and their guardians will have the opportunity to discuss questions and express their expectations for the educational program.
2	Discussion on the quantity of sugar, sodium and fat in foods. The workshop aims to clarify, using food kits, the quantities of these nutrients in foods most frequently consumed by the group. Children and families will also be taught how to read food labels correctly, to be able to take healthy decisions on daily basis.
	Educational materials will be used with drawings showing comparative food information, to illustrate how to make the best choice. The parents will receive two food guides, “In Search of a Happy Heart” and “Sodium”. In this same workshop, the children will build an educational whiteboard, with the objective of assisting in organizing the family routine. Parents and children will establish rules and routines. Regarding food, tidiness and order, for a healthy coexistence within the family. This whiteboard will be used at home to record their children’s daily behavior and teach them to self-assess their health habits.
	Directions for use:
	• choose the location where the whiteboard will be placed;
	• in the first column, set the activities;
	• the child will be evaluated daily on the activities performed, and earn a happy face at each accomplished task.
	• at the end of each month, the child will win or not a prize established by parents, depending on the nutritional pattterns during the month;
	• the prize will be awarded if the child wins at least 18 happy faces during this period.
	Suggestions:
	• it will be suggested to parents that the award is not focused on material objects, but in family activities such as going to parks or zoos, cycling or flying a kite, strengthening the family bond;
	• the whiteboard is intended to help the child to develop the idea that good habits result in good moments, not in gifts.
3	Healthy nutrition class in the kitchen. On this workshop, adults will work in the kitchen, along with the nutritionist, to prepare healthy snacks with vegetables and fruits, and learn to make substitutions in order to reduce the amount of salt, fat and sugar used at home.
	The children will receive a paper food pyramid to draw and paste the food in the right places. This workshop will also include a tale hour with the book *Correct Food.*, with an explanation about foods that are good or bad for the health. Finally, the workshop will be closed with the tasting of healthy snacks prepared by the parents.
4	Meeting with parents. In this meeting, the psychologist will conduct a team-building activity with discussions and analyses on what and how to do to change erroneous habits and attitudes in the family routine.
	In this meeting, the children will participate in a culinary workshop with the nutritionist and learn the proper technique of hand hygiene with the aid of a red washable ink. They will then prepare a “healthy orange soft drink”, with orange and papaya juice, as well as a whole grain cocoa cake. The children will also be taught about grilling, roasting and other food cooking techniques, aiming to help them have good eating habits. Finally, the children will receive a book of healthy recipes.
5	Physical activity. In this workshop, the physical educator will conduct games such as jump rope, elastic game, hopscotch, hula-hoop and video games (XBOX), so that the children and their parents exercise. The workshop aims at teaching easy exercises that do not demand much space and can be done at home. In this meeting, the children will receive lettuce seedlings to plant and create small gardens in their homes, as a means to stimulate the consumption vegetables.
6	Meeting with parents. The therapist will conduct a discussion about important points, such as how to establish limits and to deal with bullying and low self-esteem issues.
	The children will be distributed in teams for playing games about healthy eating, aiming to teach about food through the senses of touch, smell, taste and vision.
	**Vision:** fresh, whole or cut food will be shown;
	the children will be asked if they know each food presented and if they like it.
	**Tact:** the children will be blindfolded and the nutritionist will choose one food for each child,
	prompting her to handle and identify it.
	**Smell:** the child, still blindfolded, will be asked to smell and identify the food.
	**Palate:** the blindfolded child will receive a portion of the food and will be prompted to try and identify it.
	This meeting will also include other healthy eating games.
7	Meeting with parents and children. In this meeting, scenes of the movie *Muito Além do Peso* will be discussed.
8	Meeting with parents: Healthy nutrition in the kitchen: in this workshop, the guardians will join the nutritionist in the kitchen to prepare healthy dishes. The objective is to emphasize how to replace sodium, fats and sugars in food preparation.
	The children will play with the human board game, that encourages healthy habits and in which they themselves are the parts.
9	Meeting for questions and conversation. For parents and children who wish to participate, a video will be recorded on what they have learned during the meetings.
	In this last meeting, anthropometric and biochemical assessments, as well as blood pressure measurements, will be repeated in children and their guardians. All participant children will receive a certificate and a fridge magnet about “the ten healthy habits”.

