Body weight and height will be measured in duplicate by one of the researchers. Patients (children and parents) will be asked to remove shoes and heavy coats for this measurement. Nutritional status will be assessed by calculation of body mass index (BMI), with use of the Anthro Plus ® program, according to the guidelines of the World Health Organization [47,48]. BMI cut-off points for defining overweight and obesity in children will be percentile > 85 and percentile > 95, respectively, according to WHO-2006/2007 [49]. For adults, the BMI will be obtained through the relationship between total body weight in kilograms divided by height in meters squared, and will be classified according to the World Health Organization - eutrophy (BMI between 18.5 and 24.9 kg/m^2^), overweight (between 25 and 29.9 kg/m^2^), obesity I (between 30 and 34.9 kg/m^2^), obesity II (between 35 and 39.9 kg/m^2^) and obesity III (≥40 kg/m^2^) [50,51].

For children and adults, waist circumference will be measured with a measuring tape at the midpoint between the last palpable rib and the top of the iliac crest, where there is a greatest amount of visceral tissue. In children, waist circumference will be classified according to the National Health and Nutrition Examination Survey, 2003–2006 (NHANES 2003–2006), with cut-off points in the 90th percentile, according to gender and age. For adults, waist circumference cut-off points for increased cardiovascular risk will be considered as ≥94 cm for men and ≥80 cm for women, according to the World Health Organization [52].

Blood will be collected for analysis of total cholesterol, LDL-cholesterol, HDL-cholesterol and triglycerides, glucose, complete blood count and C-reactive protein after a 12 h fasting. The biochemist performing the assay will be blinded to the identity of the participants. Analyses will be conducted with an automatic enzyme technique, with Roche® kits (Brazil).

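### The final assessment is placed both in a separate eleventh meeting and inside the ninth evening workshop; the workshop placement fits poorly with the 12-hour fast and with assessor blinding for weight, waist and blood pressure

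*Protocol article*

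**What the plan says.** The paragraph of the Interventions section that introduces Table 2 sets a total of 11 meetings. It reserves two of them: "The first and the last meetings will be used for nutritional and biochemical assessment". The other nine are 90-minute weekly education workshops.

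Table 2 describes those workshops, numbered 1 to 9. Row 9 is a session for questions and conversation, with an optional video, a certificate and a fridge magnet. The same row states: "In this last meeting, anthropometric and biochemical assessments, as well as blood pressure measurements, will be repeated in children and their guardians".

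Three other statements bear on this:

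- Clock time (Interventions): "Workshops will be held in 3 different days of the week, from 6 PM to 7:30 PM".
- Blood sampling (Evaluation of outcomes): lipids, "glucose, complete blood count and C-reactive protein after a 12 h fasting".
- Blinding (Study design): the trial is a "randomized controlled, outcome evaluator-blinded parallel prospective clinical trial". Under Evaluation of outcomes, the one specific blinding statement concerns the biochemist who runs the assays. For anthropometry the text says only: "Body weight and height will be measured in duplicate by one of the researchers".

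**The concern.** The article gives two incompatible instructions for the final visit. Staff working from Table 2 would measure intervention families during an evening workshop that control families do not attend. Two consequences follow if they do.

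First, the fasting requirement becomes hard to meet, so samples may be missed or taken unfasted. Total cholesterol, LDL, HDL, triglycerides and glucose are all secondary outcomes, and total cholesterol is the variable on which the 37 per group was calculated.

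Second, whoever takes weight, waist circumference and blood pressure in that session knows the child's arm. The evaluator-blinded description then cannot be true for those measures.

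Randomisation does not protect against measurement conditions that differ by arm after allocation, and analysis cannot repair them afterwards.

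**Working it through.** **1. Meeting count.** Inputs: 11 meetings in total, assessment in the first and last, nine workshops (Interventions).

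- As the Interventions section has it: 2 assessment meetings + 9 workshops = 11. The plan's own figure is reproduced.
- With the final assessment inside workshop 9: 1 + 9 = 10. The eleventh meeting has no content.

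The row numbers in Table 2 are workshop numbers, with the opening assessment meeting not counted. The Interventions section puts the cooking-lab sessions on days 3 and 8, and rows 3 and 8 are the kitchen workshops. It also gives 18 text messages over 9 workshop weeks at two per week, 9 × 2 = 18. Row 9 is therefore the ninth workshop, which is the tenth of the 11 meetings.

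**2. Fasting.** Inputs: session from 18:00 to 19:30 (Interventions); 12 h fast (Evaluation of outcomes).

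- Earliest draw: 18:00 − 12 h = 06:00.
- Latest draw: 19:30 − 12 h = 07:30.

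A sample taken in workshop 9 that met the requirement would need a fast lasting the whole day, in children aged 7 to 11 and in their guardians. This is possible in principle, but the article makes no provision for it.

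**3. Blinding.** The measures that row 9 names, set against the blinding statements:

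| Measure in row 9 | Who obtains it | Blinding if done in workshop 9 |
|---|---|---|
| Weight, height | one of the researchers | lost: the session is intervention-only |
| Waist, blood pressure | not specified | lost, for the same reason |
| Blood assays | biochemist blinded to identity | kept, wherever the blood is drawn |

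**4. Sample size, for context.** The planning inputs are a reduction of 20 and an SD of 29.9 in total cholesterol, two-sided alpha 0.05 and power 0.80. The normal approximation is n = 2(1.96 + 0.8416)² × (29.9/20)² = 2 × 7.849 × 2.235 = 35.1, so 36 per group. The t-based solution is 36.07, rounded up to 37 as stated. The calculation reproduces and this point does not alter it.

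**5. Illustration of sensitivity.** Suppose the true effect is zero and measurement conditions alone shift one arm by d standard deviations. The two-sided t test at 5% with 37 per arm has 72 degrees of freedom and noncentrality d × √(37/2) = 4.301 d.

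| Assumed shift d | Noncentrality | False-positive rate |
|---|---|---|
| 0 | 0 | 5% |
| 0.1 | 0.43 | 7.1% |
| 0.2 | 0.86 | 13.6% |
| 0.3 | 1.29 | 24.7% |

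The values of d are assumptions with no source in the article. The table shows only how a trial of this size would respond to such a shift.

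**The case against.** A benign reading is available. Both sections speak of a last meeting, and the sentence in row 9 may describe the eleventh meeting, folded into the final row of the table. The evening hours are stated for workshops, and the Interventions section separates assessment meetings from workshops. On that reading neither the fasting problem nor the blinding problem arises. Figure 2, the timeline, is not available in the text reviewed and may show the intended visit. This objection has force: the wording is ambiguous, and the fasting and blinding consequences are conditional on following Table 2 literally. It does not remove the conflict, because the table that staff would use puts the assessment in the same row as the closing workshop.

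Four stronger readings are tempting, and the article does not support them.

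- **The primary outcomes are compromised.** Row 9 names anthropometric, biochemical and blood pressure measures only, all of them secondary. No text puts the dietary, knowledge or physical activity questionnaires in that session.
- **Controls are measured somewhere else.** The Control group section says where controls receive care, not where they are assessed. Evaluation of outcomes says both groups are evaluated at the beginning and end, and refers to Figure 2 for the schedule.
- **Baseline falls after allocation.** Study design says: "After the initial assessment, children will be randomized to either the intervention or the control groups". This agrees with the Interventions section if the first of the 11 meetings is that initial assessment, and workshop 1 in Table 2 contains no measurements.
- **The laboratory results are unblinded.** The biochemist's blinding does not depend on where the blood is drawn.

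A condensed article may also leave assessor logistics to the full protocol, and describing the measurer as a researcher does not in itself say that this person is unblinded. The blinding point therefore rests on the location given in row 9, not on missing detail.

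**Conclusion.** The point holds in a limited form. The Interventions section and Table 2 contradict each other on where the final assessment takes place, 11 meetings against an effective 10. If Table 2 is followed, blood sampling fits poorly with the 12-hour fast, and evaluator blinding fails for weight, waist and blood pressure. The conclusion on fasting assumes that the evening hours apply to the session in row 9. The conclusion on blinding assumes that measurement happens in that session.

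The reach is confined to secondary outcomes. No bias is demonstrated and its size cannot be estimated from the article, so the false-positive rates above are illustrative only. The matter still deserves correction before final assessments take place, since measurements taken under unlike conditions cannot be made comparable later.

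**What to change.** Reconcile the two places. Remove the assessment sentence from row 9 of Table 2 and hold the final assessment at the separate eleventh meeting that the Interventions section already counts. State that both arms have the same type of visit, at the same place and time of day and under the same fasting condition.

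Have anthropometry and blood pressure taken by existing staff who did not deliver that child's sessions and are not told the arm. If that cannot be arranged, limit the evaluator-blinded description in Study design to the laboratory assays.

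The cost is a change of wording and the scheduling of a visit already in the count, with minor inconvenience to families. No additional participants are needed and the sample size is unchanged.
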